## Abstract

**Background:**

Children in out-of-home care constitute a vulnerable population often experiencing mental health challenges related to early adversity and placement disruptions. The Circle of Security Parenting program^®^ (COS-P) is an attachment-based intervention designed to enhance carer sensitivity and reflective competence, ultimately improving the quality of carer-child relationships.

**Methods:**

This study protocol follows a mixed-methods randomized controlled trial evaluating the effectiveness of the COS-P program for foster carers in France. A total of 70 foster carers will be randomly assigned to either the intervention group (receiving COS-P in addition to Treatment as Usual) or the waitlist control group (receiving Treatment as Usual only). Quantitative measures, including the Caregiving Composite Questionnaire, Parenting Stress Index, and the Marschak Interaction Method, will be administered at baseline and at follow-up). Qualitative data will be collected through focus groups with foster carers and COS-P facilitators, and through self-confrontation interviews with a subset of foster carers.

**Discussion:**

This study is the first to evaluate the COS-P program for foster carers in France. Findings will provide valuable insights into the program’s effectiveness in improving carer-child relationships and foster carer well-being, ultimately contributing to better outcomes for children in out-of-home care. The study will also explore potential moderators of treatment outcome, and shed light on the subjective experiences of participants.

**Trial registration:**

This trial is registered on ClinicalTrials.gov : NCT06701877.

## Background

### Fostering Well-being: addressing the needs of children in out-of-home care

In France, the child protection system currently supports 344,682 minors and young adults, with 51% placed in out-of-home care [1].

The SAFE FAMILIES study, situated within a broader research initiative focused on promoting the mental health and resilience of children placed under the care of Child Protection Services (CPS) is a collaborative effort led by Université Lumière Lyon 2 in partnership with the Département and the Clinical Research Unit of Emile Roux Hospital of Le Puy-en-Velay.

### The vulnerability of children in foster care

A robust body of international research underscores the heightened vulnerability of children in out-of-home care. These children experience elevated rates of emotional and behavioral difficulties with an estimated 50% struggling with emotion regulation.

Further, the prevalence of mental health disorders is significantly higher in this population, with 20% experiencing at least one diagnosable psychiatric disorder [2–6].

Bronsard et al. [7] revealed high comorbidity rates and an elevated risk of post-traumatic stress disorder in children in out-of-home care compared to their peers in the general population. In a study focusing on the mental health of adolescents in residential care, Bronsard et al. [8] observed that these young people often present with atypical and less direct expressions of their psychological distress, tending to minimize or normalize their suffering. Furthermore, within the French context, the public authorities reported a high prevalence of disabilities among children in care, noting a sevenfold increase compared to the general population. Of particular concern is the predominance of psychological and mental disabilities associated with behavioral disorders [9, 10].

### Exploring the pathways to vulnerability

Understanding the complex pathways that contribute to the vulnerability of children in foster care is crucial. Most of these children have endured significant adversity, including maltreatment and disruptions in their caregiving environments [11]. Such experiences expose them to Toxic Stress, characterized by frequent, strong, and prolonged activation of the body’s stress response system [12], which can have detrimental effects on neurocognitive and emotional development (e.g., impulsivity, anxiety, difficulties with attention and concentration), social participation (e.g., challenges with peer relationships, academic performance), and both physical and mental health [13].

The psychopathological model developed by Kieling et al. [14] (see Fig. 1) provides a useful framework to understand the vulnerability of these children. This model emphasizes the accumulation of risk factors, including those related to specific developmental stages (e.g., maternal stress during the perinatal period, adolescent risk-taking behaviors), and those that are more enduring (e.g., exposure to violence, neglect, and harmful substance use).

**Fig. 1 Fig1:**
[figure not shown]
Lifecycle approach to risk factors (Kieling et al., 2011)

Furthercompounding this vulnerability, the experience of being in care can itself pose challenges. Placement instability, disruptions in caregiving relationships, institutionalization, and separation from siblings all present significant risks to children’s mental health [11]. French psychiatrist David [15], a pioneer in foster care, described the potential iatrogenic effects of separation from family, even when that family context has been maltreating, as “oister care sydrome”. This syndrome can manifest through identity disturbance, attachment difficulties, loyalty conflicts, and relational and emotional breakdowns.

Finally, access to appropriate mental health services for children in foster care within the French system can be hindered by complex administrative processes and the involvement of numerous stakeholders in each child’s case [9].

### Attachment: a foundation for resilience

Attachment theory [16] provides a critical lens to understand the developmental needs of children in foster care. Attachment is a fundamental, biologically-rooted behavioral system that promotes interpersonal regulation of stress, operating from the cradle to the grave. Secure attachment is fostered when children can confidently express their emotions, particularly negative emotions like sadness or fear, to one or more consistent and attuned caregivers. This secure base allows children to explore their world with curiosity and engage in learning.

The interplay between attachment needs and the drive for exploration is central to human development. Decades of research highlight the protective power of secure attachment for mental health. A meta-analysis by Groh et al. [17] found strong associations between secure attachment and positive outcomes such as the development of social skills (d = 0.39), a reduction in externalizing problems (d = 0.31), and a lower risk of internalizing disorders (d = 0.15).

Interventions that promote sensitive caregiving and foster secure attachments are, therefore, of great clinical importance. Such interventions can be seen as a form of “psychological vaccination», particularly crucial for children in care who, due to their experiences of adversity and relational disruptions [18, 19], are more likely to have developed insecure or disorganized attachment patterns. It is essential to remember that these insecure patterns can persist even when children are placed with new caregivers who are more sensitive to their needs [20].

### Introducing the circle of security parenting® program

Developed in the United States [21], the Circle of Security Parenting^®^ (COS-P) program is a promising attachment-based intervention designed to enhance caregiver sensitivity, parental reflective functioning, and the quality of the child’s attachment to their caregiver. This manualized intervention, with both educational and therapeutic components, empowers caregivers to better understand and respond to their child’s needs, fostering secure attachment [22].

The Circle of Security model (see Fig. 2) is central to COS-P, providing a visual representation of the child’s attachment needs and the caregiver’s role in meeting those needs.

**Fig. 2 Fig2:**
[figure not shown]
The circle of security graphic

This model highlights two essential caregiving functions:

#### Secure base

providing a safe and supportive foundation for the child’s exploration, and.

#### Safe haven

offering comfort and a secure haven when the child seeks proximity in times of stress or distress.

While the original 20-week version of the program, COS-I, includes individualized therapeutic video feedback, COS-P is a shorter, more accessible adaptation designed primarily for prevention (Cooper et al., 2009). Delivered over eight weekly group sessions (see Table 1), COS-P utilizes a manual and incorporates videos that illustrate core attachment principles and parent-child interactions. Importantly, COS-P includes an experiential dimension, encouraging participants to engage in practical exercises and reflect on their own emotional experiences within the caregiving relationship. This process of mentalization supports carers in understanding the underlying thoughts, feelings, and intentions that drive their child’s behavior.

**Table 1 Tab1:** Summary of COS-P content (from: Cassidy et al., 2017; Cooper et al., 2009/2018; Woodhouse et al., 2018 ; Maxwell et al., 2021)

COS-*P* Chapter	Key COS-*P* term/s	Core content
Chapter 1 Chapter 2	COS graphic Circle map	• Basic concepts of attachment • Children’s attachment and exploration needs • COS graphic as a map for understanding parent-child interactions
Chapter 3 Chapter 4	Being with	• Importance of being with children in their emotional states • Parent coregulating the child while the child develops their own capacity for emotion regulation
Chapter 5	Shark music	• How defensive processes (often based in the parent’s childhood experiences) can influence parents’ experience of and response to their child’s needs • Importance of parents reflecting on parenting struggles to enable more supportive responding
Chapter 6	Mean, Weak, Gone	• Hostile, helpless and neglectful parenting • Disorganized attachment • Importance of reflection to help keep caregiving in balance
Chapter 7	Rupture & Repair Time in	• Importance of relationship repair following inevitable ruptures in caregiving • How repair supports the long-term development of child emotion regulation and positive relationship capacities • “Time in” as a strategy for parent–child relationship repair
Chapter 8		• Summary of core content • Participant reflection on key learnings • Celebration of program completion

Research on COS-I has demonstrated its efficacy in improving caregiver capacities and child attachment security [23], and emerging evidence suggests the potential of COS-P as well:

Cassidy et al. [24], in a study of 141 mother-child dyads in the US, found that COS-P led to a significant reduction in insensitive maternal behaviors. Also Maxwell et al. [25] observed a significant improvement in parental reflective functioning among 221 Australian mothers of children aged from 0 to 6 years of age who participated in COS-P. Building on these promising findings, recent research has begun to explore the application of COS-P within the child protection system: Bisaillon et al. [26] found that COS-P increased reflective functioning in residential care workers. Krishnamoorthy et al. [27] reported positive outcomes for Australian foster families who participated in COS-P, including reduced carer stress, improved family relationships, and a decrease in the foster children’s emotional and behavioral difficulties.

## Methods and design

### Study aims and hypotheses

The SAFE FAMILIES study is the first evaluation in France of the Circle of Security Parenting program^®^ (COS-P) for foster carers. This attachment-based intervention is designed to enhance caregiver sensitivity and parental reflective functioning (PRF), ultimately leading to improved quality in carer-child relationships. Given the crucial role that foster carers’ emotional investment and quality of care play in promoting the well-being of children in their care, this study aims to assess the impact of COS-P on several key outcomes. This study will employ a mixed-methods randomized controlled trial (RCT) design, integrating quantitative and in-depth qualitative data. The following hypotheses will be tested:

#### Primary hypothesis (H1)

Foster carers who participate in the COS-P program will demonstrate a significant improvement in caregiving sensitivity at the 3-month follow-up assessment, as measured by the Caregiving Composite Questionnaire (CCQ). Specifically, we hypothesize that, compared to the waitlist control group, foster carers completing COS-P will, at the 3-month follow-up assessment, show.

(H1a) a greater increase in parental mentalizing,

(H1b) a greater increase in parenting self-efficacy, and.

(H1c) more positive perceptions of the child.

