### Eligibility criteria

Signed informed consent form.Commitment to attend all eight sessions of the COS-P program.Employed by CPS Haute-Loire or by one of the two participating private agencies.

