### Statistical analyses

***Sample size and analysis.*** Sample size calculation was based on an effect size of *d* = 0.38, drawn from a meta-analysis examining the impact of attachment-based interventions on parental sensitivity [49]. An a priori power analysis using G*Power software [50] indicated that 58 participants are needed to achieve 80% power with a significance level of *p* <.05. To account for potential attrition (20%), we aim to recruit 35 participants for each group (intervention and waitlist control receiving TAU).

The data will be analyzed using both quantitative and qualitative methods. Statistical analyses will be conducted using R software. All tests will be two-tailed with a significance level set at *p* <.05.

***Quantitative analyses.*** Descriptive statistics will be used to characterize the sample at baseline (T1) and at each assessment point (T2, T3). This will include frequencies and percentages for categorical variables (e.g., gender) and means and standard deviations for continuous variables (e.g., age, duration of placement). To test the primary hypothesis (H1), a two-way mixed ANOVA will be conducted with Group (Intervention vs. Control) as the between-subjects factor and Time (T1, T2) as the within-subjects factor. The dependent variable will be the CCQ score. To test the secondary hypothesis (H2), a two-way mixed ANOVA will be conducted with Group (Intervention vs. Control) as the between-subjects factor and Time (T1, T2) as the within-subjects factor. The dependent variable will be the PSI score. To explore the potential moderating effects of parental burnout (PBA), perceived emotional support from placement services (SAQ) and fidelity of program implementation, hierarchical multiple linear regressions will be performed. The CCQ and PSI scores at T2 will be the dependent variables, with group allocation (Intervention vs. Control) as the primary predictor. The potential moderators (PBA, SAQ, and fidelity of implementation) will be entered in the model after the main effect of group allocation.

Complementary Analyses for a Subgroup of Foster Carers: A subgroup of 20 foster carers will participate in additional assessments using the Parent Development Interview - Revised (PDI-R) and the Marschak Interaction Method (MIM) coded with the Dyadic Emotional Interaction Style (D-EIS). These assessments will be conducted at T1 (baseline) and T2 (3-month follow-up).

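### H1 is worded for carers completing COS-P while its test compares the allocated groups; if the H1 wording governs, a post-randomisation condition falls on one arm and can bias the primary comparison

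*Protocol article*

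**What the plan says.** The article describes the intervention side of the primary question in three ways.

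- Primary hypothesis (H1), lead sentence: "Foster carers who participate in the COS-P program will demonstrate a significant improvement in caregiving sensitivity at the 3-month follow-up assessment".
- Primary hypothesis (H1), specification of H1a to H1c: "compared to the waitlist control group, foster carers completing COS-P will, at the 3-month follow-up assessment, show" the listed gains. The waitlist side carries no matching condition, and completing is not defined.
- Statistical analyses: "To test the primary hypothesis (H1), a two-way mixed ANOVA will be conducted with Group (Intervention vs. Control) as the between-subjects factor", with Time (T1, T2) as the within-subjects factor. The moderator regressions on T2 scores are specified "with group allocation (Intervention vs. Control) as the primary predictor".

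Randomisation takes place at T0 (Randomization), before baseline and before any session. T2 falls three months after the final session (Measures). On losses, the Statistical analyses section says: "To account for potential attrition (20%), we aim to recruit 35 participants for each group".

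**The concern.** Whether a carer finishes the course is known only after randomisation, and only a carer offered the course can fail to finish it. Comparing completers with an unrestricted waitlist arm sets a selected group against an unselected one. If those who stop would have changed differently on the CCQ from those who finish, the difference between groups contains that selection as well as any effect of COS-P. The article itself treats burnout and perceived support as possible influences on outcome, and either could plausibly also affect who stops.

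The wording matters because it defines the primary question. An analysis plan written from the H1 sentence would analyse completers; one written from the Statistical analyses section would analyse carers as allocated. The Discussion looks ahead to including COS-P in pre-service or continuing education. That decision needs the effect of offering the course.

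A second, distinct matter is the named method. A standard mixed ANOVA with two time points needs both T1 and T2, so a carer without T2 contributes nothing.

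**Working it through.** **1. The plan's own figure.** The article states "Sample size calculation was based on an effect size of *d* = 0.38" and that "58 participants are needed to achieve 80% power with a significance level of *p* <.05". For a within-between interaction with 2 groups and m = 2 times, f = d/2 = 0.19 and λ = f²·N·m/(1−ρ). The article gives no correlation; assuming ρ = 0.5, λ = 0.0361 × 58 × 2/0.5 = 8.38 and power is 0.812 (0.798 at N = 56). So 58 reproduces. With 20% attrition, 70 × 0.8 = 56 carers would have both measurements, 28 per arm if losses are equal. Whether that calculation suits the planned comparison is a separate question.

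**2. Who is compared.**

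| Place | Intervention side | Control side |
|---|---|---|
| H1, lead sentence | carers who participate | not named |
| H1, specification of H1a–c | carers completing | waitlist group, no condition |
| Statistical analyses, ANOVA | Intervention | Control |
| Statistical analyses, regressions | allocated to Intervention | allocated to Control |

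The second row is the only one that sets a completion condition, and it sets it on one side.

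**3. Size if the second row governed.** Assumptions, none from the article: true effect zero; 35 per arm; change in SD units; all controls retained; a share q of the intervention arm left out.

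*Model A.* Those left out have the lowest values of a normal variable correlated r with CCQ change. Shift = r·φ(z_q)/(1−q), with standard error √(1/[35(1−q)] + 1/35). At q = 0.20, φ(z_q) = 0.280 and 0.280/0.80 = 0.350. With r = 0.5 the shift is 0.175, the standard error is √(1/28 + 1/35) = 0.254, and the two-sided rejection rate is 10.6%.

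*Model B.* Would-be stoppers' mean change is lower by δ, with SD 1 within each subgroup. Removing them from one arm gives a shift of q·δ; at q = 0.20, 0.20 × 0.5 = 0.10 and 0.20 × 1.0 = 0.20. Rejection rates come from 10,000 simulated trials per setting with a two-sample t-test.

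| q | A: shift at r = 0 / 0.2 / 0.5 | A: rejection | B: shift at δ = 0.5 / 1.0 | B: rejection |
|---|---|---|---|---|
| 10% | 0 / 0.04 / 0.10 | 5% / 5.3% / 6.8% | 0.05 / 0.10 | 5.1% / 6.6% |
| 20% | 0 / 0.07 / 0.175 | 5% / 5.9% / 10.6% | 0.10 / 0.20 | 6.9% / 10.4% |
| 30% | 0 / 0.10 / 0.25 | 5% / 6.6% / 15.6% | 0.15 / 0.30 | 8.4% / 17.2% |

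For scale, 0.20/0.38 = 53% of the planning effect. The two figures share a unit only when the T1–T2 correlation is 0.5, since the SD of change is √(2(1−ρ)) score SDs.

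**4. Loss of T2 in the ANOVA.** This removes carers from both arms. If loss is equal and arises in the same way in each, the two shifts cancel under no true effect. If it differs, the difference of the two shifts remains: under model A with r = 0.5 in both arms, 30% loss against 10% gives 0.25 − 0.10 = 0.15 SD.

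**The case against.** A reader might infer that the plan removes carers who stop COS-P and that the primary result is therefore biased in favour of the programme. The documents do not support that.

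- No passage excludes non-completers from the ANOVA. The arms are formed by random assignment, the test uses Intervention vs. Control, and the regressions say group allocation. H1 can be read as loose hypothesis prose.
- Table 3 schedules the CCQ at T1 and T2 with no arm or attendance condition, and Table 4 lists the quantitative measures for both groups with N = 70. The carer questionnaires are online, so a carer who stops can still answer.
- "Commitment to attend all eight sessions of the COS-P program" is an entry criterion for every carer, not a rule for removing anyone. Together with the individual make-up sessions, it may keep stopping low.
- Missing T2 data affect both arms, and the 20% allowance is applied to each. This should not be merged with one-arm selection.
- The direction is open. Stressed carers may start lower on the CCQ, but the analysis concerns change, and they may have more room to improve.
- An analysis set and missing-data rules may stand in a full protocol or analysis plan that is not shown. Their absence from the article is no fault.

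All of this stands, and it limits the point to a conditional one. It does not remove the completer wording from the primary hypothesis, its conflict with the test of that hypothesis, or the complete-case nature of the method the article names.

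**Conclusion.** The primary hypothesis and its planned test disagree on who is compared. If the H1 wording governs, the comparison can be biased by selection in one arm. At 20% exclusion from the intervention arm with all controls kept and no true effect, the shift is 0 to about 0.2 SD of change and the type I error 5% to about 10%. The lower end applies when stopping is unrelated to CCQ change. The upper end needs a correlation of about 0.5, or a 1 SD deficit in change among stoppers; the documents give neither. They also give no stopping rate: their 20% is general attrition. If the allocated groups govern, this mechanism does not arise. What remains is a complete-case analysis in both arms, biased only if loss of T2 distorts the comparison.

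**What to change.** 1. In H1, replace carers completing COS-P with carers allocated to COS-P, and bring the lead sentence into line, so that hypothesis and test name the same groups.
2. State that all randomised carers are analysed in their allocated arm whatever their attendance.
3. Replace the two-time mixed ANOVA with a likelihood-based T1–T2 model (constrained longitudinal or mixed model), so that carers with only T1 contribute. This relies on missingness being explained by arm and observed scores; it does not remove bias from loss that depends on the unseen T2 value.
4. If an effect in completers is of interest, keep it as a labelled secondary analysis with completion defined in advance.

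The cost is wording and slightly more analysis work. The sample size and data collection schedule need no change. The estimate may be smaller than a completer estimate would be.
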